## 4 Objectives

### 4.1 Study Objectives

The primary objective of the study is to assess the efficacy of an evidence-based, cognitive-behavioral, culturally adapted, lay-provided intervention on mental health outcomes of adult Venezuelan migrants living in Lima. Furthermore, the primary objective is to assess changes in outcomes in depression, anxiety and PTSD symptoms. We expect to see a trend towards less

Adaptation and assessment of a common element treatment protocol designed to improve mental health in forcibly displaced populations  
depression, anxiety and PTSD over time. Version 1, September 17, 2024

The secondary objective is to assess the feasibility and acceptability of such an intervention. Moreover, the secondary objective is to measure the recruitment rate, retention rate, fidelity and acceptability by providers and participants.

The exploratory objective is to assess the moderating effect of experiences in migration, integration and demographic variables on the efficacy of the intervention. Another exploratory objective is to identify characteristics associated with success of the implementation.

## 4.2 Study Outcome Measures

### 4.2.1 Primary Outcome Measures

Since the intervention is transdiagnostic and addresses several CMD, there will be three primary outcome measures. Changes in anxiety will be measured using the GAD7 scale. This is a 7-item instrument that measures generalized anxiety. Changes in depression will be assessed using the PHQ9 questionnaire, which is a 9-item instrument that measures depression. Both instruments have been chosen because they are short, easy to administer and have been widely used in research. Spanish versions of GAD7 and PHQ9 have been validated and used in Venezuelan and Peruvian populations. Furthermore, prior studies with this same population conducted by the main researcher have used these instruments. Regarding PTSD, changes will be measured using the PCL5 checklist which has been validated for its use in Spanish-speaking populations and utilized in research projects with similar populations. The LEC5, which identifies potentially traumatic events in the life course of the participants, will be used at baseline and in the follow-up assessments along with the PCL5.

The primary outcomes will be measured at baseline during screening and at endline 12 weeks after baseline in the case of waitlist control. In the intervention group, they will be assessed at baseline during screening, weekly (PCL5) or every two weeks (PHQ9 and GAD7) throughout the intervention before the next session, after the last session of the intervention and at 1-, 3-, and 6-month follow-ups after completion of the intervention. Participants will be sent a secure REDCap link, where they will be asked to answer each item of the instruments.

See appendix with the English and Spanish versions of the instruments.

### 4.2.2 Secondary Outcome Measures

Additionally, the feasibility and acceptability of the intervention will be secondary outcomes. Recruitment rate, reasons for not participating, retention rate, fidelity and acceptability by providers and participants will be measured. Regarding fidelity, the providers will perform an adherence checklist and audio record their sessions. Research staff will assess 20% of the recorded sessions for adherence and competence. Regarding acceptability, providers and participants will complete a participant satisfaction assessment for each session. The following instruments will be used to measure the secondary outcomes:

- Feasibility:
  - o Recruitment:
    - % of participants who consent to screening
    - % who are eligible who enroll
    - characteristics of refusers and reasons for refusal

Adaptation and assessment of a common element treatment protocol designed to improve mental health in forcibly displaced populations

Version 1, September 17, 2024

- % who meet eligibility
- reasons for ineligibility
- % ineligible for each criterion
- Retention:
  - X enrolled who completed all study visits and follow-up assessment
- Fidelity:
  - Adherence scores in provider checklist
  - Adherence and competence scores (0 to 10) from research staff assessment of audio recorded sessions
- Acceptability:
  - Provider perception (assessed after each session):
    - Perception of satisfaction of the participant in the session's helpfulness, enjoyment and relevance (0 to 10)
    - Plans to use material learned in the future (Yes/No)
  - Participant perception (assessed after each session):
    - Direct participant report on the satisfaction in the session's helpfulness, enjoyment and relevance (0 to 10)
    - Plans to use material learned in the future (Yes/No)

Acceptability measures will be collected after each session via a REDCap secure link-sent to each provider and participant by the research team.

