| Design/Methodology:             | 
Migrants will be randomized to receive the intervention (<math>n = 60</math>) or wait list control (<math>n = 30</math>). Mental health outcomes (PHQ9, GAD7, PCL5) will be assessed at baseline during screening, throughout the intervention, post treatment, and at 1-, 3-, and 6- months follow-up. Demographic information, the IPL will be assessed at the time of enrollment. LEC5 will be assessed at baseline and at 1-, 3- and 6-month follow-up. Acceptability will be assessed after each session. All assessments will be conducted by the research team through a secure link in REDCap. Each migrant will participate in 5 assessment sessions and 6-12 intervention sessions with prior assessment of mental health outcomes. The intervention sessions have a frequency of once a week. In the case of the waitlist control, mental health outcomes will be assessed at baseline at the time of enrollment and at endline 12 weeks after baseline. Once the endline has been assessed, they will receive the intervention, with corresponding assessments as described previously. In the case of the providers, feasibility and acceptability will be assessed after each session. See Appendix for a graph of the design, schedule and assessments.
 |

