## 8 Study Intervention

The intervention in the present study was developed based on CBT techniques that have proven effective in the treatment of CMD. The intervention underwent a process of cultural adaptation following the Ecological Validity Model developed by Bernal et al. (1995), which has been used in numerous adaptations of psychosocial interventions, for instance by Perera et al. (2020 and 2022) in the adaptation of Problem Management Plus for its implementation with Venezuelan migrants in Colombia. In the following paragraphs we describe the intervention that resulted from this process. Figure 1 synthesizes its components:

[figure not shown]

Figure 1. Intervention components and implementation strategies.

In terms of the implementation, the intervention will be free of cost for the participant. It will comprise between 6 and 12 weekly sessions in consecutive weeks and will be delivered remotely via a video call. The sessions will last 60 minutes and before each session participants will be sent a link to REDCap to fill out the questionnaires for the measurement of the primary outcomes. After the session they will answer questions on the session’s acceptability. Since it has been identified that Venezuelan migrants have long working days and might also work in the weekends, we will offer many possibilities to schedule the sessions (e.g. Sundays, early in the morning, late at night...). There will be some flexibility will sessions cancellations and re-scheduling. However, at the beginning of the intervention some rules in this regard will be

Adaptation and assessment of a common element treatment protocol designed to improve mental health in forcibly displaced populations  
 Version 1, September 17, 2024  
 agreed upon between provider and participant. A general rule will be set in place and participants will be told that if they can re-schedule a maximum of three sessions in a row and of six sessions overall throughout the intervention. Otherwise, they will be excluded from the study

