|-------------------------------------|--------------------------------------------------------------------------------------------------------------------------------------------------------------------------------------------|-------------------------------------------------------------------------------------------------------------------------------------------------------------------------------------------------------------------|
|                                     | May-August 2025

Third group of 30 participants:
August -November 2025                                                                                                            |                                                                                                                                                                                                                   |
| Sessions 7 to 12                    | First group of 30 participants:
May - August 2025

Second group of 30 participants:
August-November 2025

Third group of 30 participants:
November 2025-February 2026 | Individually with provider
Remotely via Meet or WhatsApp videocall
60 min duration
Focus on other aspects relevant to mental health (emotional regulation, problem solving, adaptation related distress) |
| Assessments throughout intervention | January 2025 to February 2026                                                                                                                                                              | Remotely via REDCap secure link (PCL5 every week before the session, PHQ9 and GAD7 every 2 weeks before the session, acceptability and adherence every week after each session)                                   |
| Endline                             | May 2025 to February 2026                                                                                                                                                                  | Remotely via REDCap secure link (PHQ9, GAD7, LEC5 and PCL5)
12 weeks after first session in intervention group (or within 14 days of completion).
12 weeks after baseline in waitlist control group.        |

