| Assessment at 1-month follow-up     | August 2025 to January 2026                                                                                                                                                                | Remotely via REDCap secure link (PHQ9, GAD7, LEC5, PCL5) one month after endline (or a maximum of a month later).                                                                                                 |
| Assessment at 3-month follow-up     | October 2025 to March 2026                                                                                                                                                                 | Remotely via REDCap secure link (PHQ9, GAD7, LEC5, PCL5) three months after endline (or a maximum of a month later).                                                                                              |
| Assessment at 6-month follow-up     | January to June 2026                                                                                                                                                                       | Remotely via REDCap secure link (PHQ9, GAD7, LEC5, PCL5) 6 months after endline (or a maximum of a month later).                                                                                                  |
| Data Analysis                       | June 2026 to July 2027                                                                                                                                                                     | Data analysis will take place using data analytic software and be used for publication and dissemination in scholarly journals and conferences.                                                                   |

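### Acceptability is rated only after sessions that take place, so people who never start give no rating, early stoppers give few, and the reported level is likely, though not certainly, too high

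*Protocol*

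**What the plan says.** Four places in the protocol tie acceptability to the session:

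- Section 4.2.2: "providers and participants will complete a participant satisfaction assessment for each session", and "Acceptability measures will be collected after each session via a REDCap secure link-sent to each provider and participant by the research team". The participant items are a "Direct participant report on the satisfaction in the session's helpfulness, enjoyment and relevance (0 to 10" scale and a yes/no item on future use of the material.
- Section 2 (Design/Methodology): "Acceptability will be assessed after each session".
- Section 8: "After the session they will answer questions on the session", referring to its acceptability.
- Section 12 (assessments throughout intervention): "acceptability and adherence every week after each session".

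The later assessments carry no acceptability item. The endline row of section 12 reads "Remotely via REDCap secure link (PHQ9, GAD7, LEC5 and PCL5", and the 1-month row reads "Remotely via REDCap secure link (PHQ9, GAD7, LEC5, PCL5) one month after endline (or a maximum of a month later". The 3- and 6-month rows list the same four instruments.

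No exit rating is described. Under section 9.1.2, participants who miss a session are called to learn of difficulties and to reschedule, and those who exceed the re-scheduling limit leave the study. Reasons for not taking part are recorded at the consent call (section 11), which comes before enrolment.

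**The concern.** Acceptability is a stated secondary objective (section 4.1), and section 5 says that all randomized subjects enter the analyses. The instrument, however, reaches a person only while that person is attending. Someone who finds the treatment unacceptable and leaves after one session is asked once, before or around the time of deciding to leave. Someone who never joins a session is not asked at all.

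A link between stopping and acceptability is plausible in this population. Section 8 reports a common belief that talking about distress makes it worse, and section 6.3 allows that distress may rise at first. If such people leave early, the ratings describe mainly those whom the treatment suited. The schedule is fixed in the protocol, so an analysis plan can choose how to average but cannot supply ratings that nobody requested.

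**Working it through.** **The plan's own figures.** The protocol states no acceptability target, dropout rate or non-start rate. Its one calculated figure, n = 59 in section 15.2, reproduces if 95% confidence is assumed: ln(0.05)/ln(0.95) = 58.40, rounded up to 59. It does not bear on this point.

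**What follows without assumptions.** Ratings per participant are 0 for a never-starter, at most 2 for someone who stops after two sessions, and 6 to 12 for a completer (session range from section 8).

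**Illustration (all rates and scores assumed).** Let a be the share who never start, e the share who stop after 2 sessions, and S = 6 or 12 the sessions of a completer. Completers rate 8. Non-completers rate, or would rate, m.

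- Mean over ratings = [2e·m + S(1−a−e)·8] / [2e + S(1−a−e)]
- Mean over raters, one value per person = [e·m + (1−a−e)·8] / (1−a)
- Mean over everyone offered treatment = (a+e)·m + (1−a−e)·8

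Worked case with a = 0.10, e = 0.20, m = 6, S = 6 and 90 people (9 never start, 18 stop early, 63 complete):

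- Over ratings: (36×6 + 378×8)/414 = 7.83
- Over raters: (18×6 + 63×8)/81 = 7.56
- Over all: (27×6 + 63×8)/90 = 7.40
- Non-completers are 30% of people but give 36/414 = 8.7% of ratings (36/792 = 4.5% if S = 12).

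| a / e | m | Over ratings (S = 6 to 12) | Over raters | Over all | Total gap | Due to averaging | Due to never-starters not being asked |
|---|---|---|---|---|---|---|---|
| 5% / 10% | 6 | 7.92 to 7.96 | 7.79 | 7.70 | 0.22 to 0.26 | 0.14 to 0.17 | 0.09 |
| 5% / 10% | 5 | 7.89 to 7.94 | 7.68 | 7.55 | 0.34 to 0.39 | 0.20 to 0.26 | 0.13 |
| 10% / 20% | 6 | 7.83 to 7.91 | 7.56 | 7.40 | 0.43 to 0.51 | 0.27 to 0.35 | 0.16 |
| 10% / 20% | 5 | 7.74 to 7.86 | 7.33 | 7.10 | 0.64 to 0.76 | 0.41 to 0.53 | 0.23 |
| any | 8 | 8.00 | 8.00 | 8.00 | 0 | 0 | 0 |

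Differences are taken before rounding. The averaging part disappears once each person counts once. The last column remains under any averaging rule. It treats a never-starter as having a would-be rating, which is a device for showing scale and not something that could be observed.

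**A case that shows averaging only.** Suppose 20% to 40% stop after 2 sessions and rate 5, the rest attend 9 sessions and rate 8.5, and nobody fails to start.

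- 20%: over ratings (0.2×2×5 + 0.8×9×8.5)/(0.4 + 7.2) = 8.32; over persons 7.80.
- 40%: over ratings (0.4×2×5 + 0.6×9×8.5)/(0.8 + 5.4) = 8.05; over persons 7.10.

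The gap of 0.5 to 0.9 comes wholly from the averaging rule, because every early stopper in this case was asked and answered.

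**The case against.** Rating each session at once limits recall error and is a legitimate choice. Anyone who attends even once is asked, and the provider gives a second view of that participant's satisfaction. Dropout is not hidden: section 4.2.2 reports retention, and section 15.3 places attendance and assessment completion beside the acceptability ratings and tabulates reasons for missing data. Section 9.1.2 names long working hours and family duties as pressures on attendance, and the number of sessions varies by design with symptoms, so few ratings need not mean low satisfaction. The averaging rule is not fixed and may be set in an analysis plan. The existing items concern a session and what was learned in it, so they do not suit someone who attended none. Scoring every non-rater as a rejection would replace a possible upward bias with a downward one.

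All of this stands, and it rules out three stronger readings. A reader might infer that the acceptability result is certain to be inflated, but the documents do not show that stopping follows dissatisfaction. A reader might take a gap of 0.5 to 0.9 points as the size of the design's bias, but that figure reflects averaging on data already collected. A reader might conclude that the trial can say nothing about acceptability, but attendance and retention will be reported beside the ratings.

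What remains is that those measures show who left, not how they judged the treatment overall, and no later analysis can fill that gap.

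**Conclusion.** The point holds in limited form. Collection is confined to sessions that take place, so never-starters are unrated and early stoppers are thinly represented. If dissatisfied people stop sooner, the reported acceptability is likely too high; if stopping is unrelated to satisfaction, the excess is zero. The present design cannot tell these two situations apart.

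The size cannot be computed from the protocol. With 5% to 10% assumed never to start, 10% to 20% assumed to stop after two sessions, and non-completers assumed to rate 2 to 3 points lower, the mean over ratings is about 0.2 to 0.8 points too high. Of that, 0.1 to 0.2 points would survive per-person averaging. This concerns a secondary objective of a pilot and leaves the primary efficacy comparison untouched.

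**What to change.** Keep the session ratings and make these additions in sections 4.2.2 and 12:

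1. Add a short overall acceptability rating, worded about the treatment as a whole, and a reason-for-stopping item to the existing endline (post-treatment) REDCap link.
2. Send it to everyone offered treatment, including those who stopped early and those removed under the re-scheduling rule. For waitlist participants, use the assessment after their own treatment, because their 12-week endline comes before it.
3. Give never-starters the reason item only, at a defined contact point (for example 12 weeks after the offer), since the endline row is timed from the first session or from completion.
4. Report one acceptability value per participant, with the number offered treatment and the number without a rating, beside attendance and retention.
5. If non-raters are also counted as not acceptable, label that line as a worst-case bound and not an estimate.

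The cost is one or two extra minutes per participant on a link that already exists, plus one added contact for never-starters. Response from those who stopped will be incomplete, so the number without a rating must be shown. The change has to be made prospectively.

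### Provider acceptability is a stated secondary outcome, but its only graded measure is the provider's impression of the participant's satisfaction, and the one other provider item does not say whose plans it records

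*Protocol*

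**What the plan says.** Protocol 4.1 states that "the secondary objective is to measure the recruitment rate, retention rate, fidelity and acceptability by providers and participants". Section 4.2.2 repeats this as an outcome: "fidelity and acceptability by providers and participants will be measured". The Protocol Summary (Design/Methodology) says: "In the case of the providers, feasibility and acceptability will be assessed after each session". Section 15.3 includes acceptability, as rated by each of the two groups, among the variables for regression.

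Section 4.2.2 then says how it is measured. The lead-in reads "providers and participants will complete a participant satisfaction assessment for each session". Under provider perception there are two items: "Perception of satisfaction of the participant in the session", covering helpfulness, enjoyment and relevance on a 0 to 10 scale, and "Plans to use material learned in the future (Yes/No"). Under participant perception the first item is "Direct participant report on the satisfaction in the session", on the same three aspects and the same scale. The second repeats the Yes/No item word for word.

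Section 14.2 lists an Acceptability form among the case report forms in the Appendix. That Appendix is not in the text available for this review.

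**The concern.** The objective names two groups whose acceptance is to be measured. For participants the graded item asks for their own view. For providers it asks for an estimate of the participant's view. A result reported as provider acceptability would then describe something other than what its label says.

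This matters because the intervention is meant for lay delivery. Section 3.1 presents it as a resource for community leaders, shelter workers, NGOs and primary-level staff, so whether lay people find it acceptable to deliver is a natural question for the pilot. Section 7.1 enrols the lay providers as study participants in their own right. Section 6.1 foresees that they may find session content upsetting or worry about participants. The protocol handles that through supervision, which is not listed as an outcome.

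**Working it through.** The protocol gives no sample size, threshold or other figure for provider acceptability, so there is nothing to reproduce. The check is a comparison of what is promised with what is collected.

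1. **What is promised.** Sections 4.1 and 4.2.2 use one phrase for both groups: "fidelity and acceptability by providers and participants". For participants this plainly means their own acceptance. Read in parallel, it means the same for providers.

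2. **What is collected from providers.** Section 4.2.2 has two bullets.
   - The 0 to 10 rating has the participant's satisfaction as its object. It is a proxy rating, and it is the only graded provider measure: 1 of 1 graded measures is a proxy.
   - The Yes/No item can be read in two ways. If it means the provider's plans, it is a first-person indicator of intended use, but binary and silent on helpfulness, enjoyment and relevance. If it means the participant's plans as the provider sees them, it is a second proxy. The wording does not decide. The item is identical in both lists, and learning the material fits both the participant who is taught it and the provider who was trained in it.

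3. **Count.** Items that give the provider's own view: 0 of 2 under the second reading, 1 of 2 under the first.

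4. **What a score would mean.** A provider who finds the sessions hard to deliver but believes the participant was pleased would score high. A provider who likes delivering the material but believes the participant was bored would score low. The scale need not follow the provider's own acceptance in either direction.

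5. **Whether it can be repaired later.** The gap lies in the question asked after the session. An analysis plan can rename the variable, but it cannot supply a rating that was not collected.

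**The case against.** The strongest reply is that section 4.2.2 describes a deliberate two-informant design. The lead-in says openly that both groups assess participant satisfaction, and the two lists contrast a perception with a direct report. Section 15.3 speaks of acceptability rated by providers, which makes them raters. On that reading nothing is hidden and only the label is loose. The form in the Appendix may also be worded differently from the shorthand in 4.2.2. Finally, the protocol ties no threshold or progression decision to provider acceptability.

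Much of this stands. The proxy rating is legitimate data. A reader might call it a duplicate of the participant's rating, but it is a second informant's view, and disagreement between provider and participant is informative. It should be kept. A reader might also count three proxy items out of four. The text supports only two bullets and does not say whether the first yields one score or three.

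The rater reading fits the lead-in and section 15.3 better than it fits section 4.1, where providers stand beside participants as a group whose acceptance is sought, or the Summary, which presents acceptability as something assessed for the providers. If providers were meant only as raters of participant satisfaction, those passages would need to say so. If the form already asks for the provider's own view, section 4.2.2 still has to be brought into line with it.

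**Conclusion.** The point holds as a minor one about measurement. In the protocol text, provider acceptability rests on one proxy scale and one ambiguous Yes/No item, so a high score would show mainly that providers believe participants were satisfied.

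A reader might go further and infer that the trial cannot report provider acceptability at all. The document does not support that. The Yes/No item sits under provider perception and, if it refers to the provider's own plans, gives a limited direct indicator after every session.

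The conclusion assumes that section 4.2.2 reflects the form providers will complete and that acceptability by providers means their own acceptance. Primary outcomes, randomisation and safety monitoring are not affected.

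**What to change.** In section 4.2.2 and in the provider version of the Acceptability form:

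- Add a 0 to 10 rating of the provider's own view of delivering the session: helpfulness of the material, enjoyment in delivering it, and relevance. State whether this is one score or three, and report it as provider acceptability.
- State that the Yes/No item refers to the provider's own plans.
- Keep the existing proxy rating, and name and report it separately as provider-perceived participant satisfaction. This preserves the comparison with the participant's direct report.

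The cost is a slightly longer form after each session. The Protocol Summary plans 9 participants per provider and 6 to 12 sessions each, so at full attendance the addition appears on 9 × 6 = 54 to 9 × 12 = 108 forms per provider. Relabelling the outcome alone would be cheaper, but it would leave the stated objective unmet unless the Protocol Summary and sections 4.1, 4.2.2 and 15.3 were changed as well.
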